## Abstract

**Background:**

Patients with intracranial tumors are more sensitive to anesthetics than the general population and are therefore more susceptible to postoperative neurologic and neurocognitive dysfunction. Sevoflurane or propofol combined with remifentanil are widely used general anesthetic regimens for craniotomy, with neither regimen shown to be superior to the other in terms of neuroprotective efficacy and anesthesia quality. There is no evidence regarding the variable effects on postoperative neurologic and neurocognitive functional outcome under these two general anesthetic regimens. This trial will compare inhalational sevoflurane or intravenous propofol combined with remifentanil anesthesia in patients with supratentorial gliomas and test the hypothesis that postoperative neurologic function is equally affected between the two regimens.

**Methods:**

This is a prospective, single-center, randomized parallel arm equivalent clinical trial, which is approved by China Ethics Committee of Registering Clinical Trials (ChiECRCT-20,160,051). Patients with supratentorial gliomas diagnosed by magnetic resonance imaging will be eligible for the trial. Written informed consent will be obtained before randomly assigning each subject to either the sevoflurane-remifentanil or propofol-remifentanil group for anesthesia maintenance to achieve an equal-desired depth of anesthesia. Intraoperative intervention and monitoring will follow a standard anesthetic management protocol. All of the physiological parameters and other medications administered during the intervention will be recorded. The primary outcome will be neurologic function change assessed by National Institute of Health Stroke Scale (NIHSS) within 4 h after general anesthesia when observer’s assessment of alertness/sedation (OAA/S) reaches 4. Secondary outcomes will include NIHSS and modified NIHSS change 1 and 2 days after general anesthesia, hemodynamic stability, intraoperative brain relaxation, quality of anesthesia emergence, quality of anesthesia recovery, postoperative cognitive function, postoperative pain, postoperative neurologic complications, as well as perioperative medical expense.

**Discussion:**

This randomized equivalency trial will primarily compare the impacts of sevoflurane-remifentanil and propofol-remifentanil anesthesia on short-term postoperative neurologic function in patients with supratentorial gliomas undergoing craniotomy. The exclusion criteria are strict to ensure that the groups are comparable in all aspects. Repeated and routine neurologic evaluations after operation are always important to evaluate neurosurgical patients’ recovery and any newly presenting complications. The results of this trial would help specifically to interpret anesthetic residual effects on postoperative outcomes, and perhaps would help the anesthesiologist to select the optimal anesthetic regimen to minimize its impact on neurologic function in this specific patient population.

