Inhalational anesthesia and intravenous anesthesia are widely used in current neurosurgical anesthesiology [2], and sevoflurane combined with remifentanil or propofol combined with remifentanil are both accepted as general anesthesia strategies. Comparative studies have been done to investigate the effects of different anesthetics on craniotomies [3], both primary and secondary outcomes focused on the changes in intraoperative physiological parameters [3, 4], laboratory results [3], and anesthesia recovery indices during emergence [5, 6]; however, neuronal disease-specific study is lacking, and there is no evidence related to how postoperative neurological function and neurocognitive outcomes are affected by different general anesthesia strategies [7]. Patients with neurological diseases, e.g., brain tumors, are usually excluded in studies examining the correlation between anesthesia and neural function [8], as those diseases are major confounders leading to nervous system dysfunction, however, anesthetic effects on neural function cannot be ignored in neurosurgical patients, let alone the previously mentioned “vulnerable” brain tumor patient who is even more susceptible to anesthetics [9]. Recent findings have reported patients with supplementary motor area (SMA) lesions presenting with intraoperative neurological deficits for awake craniotomy which could not be explained anatomically by their intact corticospinal tracts as detected by cortical stimulation or cortical mapping [10, 11], and these deficits were reversible after operations over time without further intervention. Although this finding may have been related to lesion location, which is called “SMA symptom”, this phenomenon cannot exclude the possibility of residual anesthetic-induced neurological deficits in both the intraoperative and early postoperative periods.

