### Populations

Adult male and female patients scheduled for elective craniotomy under general anesthesia with supratentorial (frontal-parietal-temporal) gliomas diagnosed by magnetic resonance imaging (MRI) are eligible for the study. All patients must sign institutional approval and informed consent before enrollment, the written informed consent will be obtained 1 day or a few days before operation, when patients are seen by anesthesiologists in the ward. The information and reasons why eligible patients are not recruited to the trial will be documented. The inclusion and exclusion criteria are listed in Table 1.

**Table 1 Tab1:** Inclusion and exclusion criteria

Inclusion Criteria	
Patients aged between 18 to 65 years old with American Society of Anesthesiology (ASA) status I ~ II who are scheduled for elective craniotomy for the treatment of supratentorial gliomas must fulfill the following:	
1	Frontal-Parietal-Temporal glioma diagnosed by preoperative MRI
2	Glasgow score of 15 without preoperative symptomatic elevated intracranial pressure
3	New and/or recurrent intracranial gliomas are allowed
Exclusion Criteria	
1	Unable to comprehend and cooperate with the neurologic examination
2	Emergency craniotomy or changed to emergency from elective craniotomy
3	Insular lobe is invaded by glioma
4	Scheduled intraoperative motor evoked potential monitoring
5	Patients with traumatic brain injury, intracerebral hemorrhage, or cerebral vascular diseases
6	Patients with prolonged emergence, postoperative mechanical ventilation, and/or sedation dependence due to a definite reason (e.g., surgery itself or tumor location)
7	Hypothalamic dysfunction
8	Radiotherapy and/or chemotherapy before surgery
9	Uncontrolled hypertension or severe heart disease that impairs cardiac function (New York Heart Association Functional Classification ≥ III)
10	History of related anesthetic allergy
11	Severe endocrine system dysfunction that impair metabolic index
12	Impaired mental status
13	Drug and/or alcohol abuse
14	Pregnant and/or lactation period patients
15	Neuromuscular diseases
16	Infectious and/or immune diseases with positive biomarker(s)
17	Body mass index > = 35

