### Randomization and blinding

Permuted-block randomization will be used with a block size of 4 and an allocation ratio of 1:1 to either sevoflurane-remifentanil group or propofol-remifentanil group. Random allocation sequence will be based on a computer-generated random digits table. One investigator who will not participate in anesthetic management or follow-up will implement the randomization and enroll patients, and allocation will be concealed in a sealed opaque envelope until patient enters the operating room. Randomization will occur for patients conforming to the above criteria, and written informed consent will then be obtained from themselves or their next-of-kin. Since the two general anesthetic administration routes are distinct (inhalational versus intravenous), patients and anesthesiologists cannot be blinded. An independent team who is not involved in the intraoperative management will be in charge of postoperative follow-up and is blinded to the intervention.

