#### Outcomes

Patients will have been screened 1 to 2 days before operation, and the demographic characteristics, clinical manifestations, and past history obtained at this time. Detailed descriptions of the lesion in MRI will be obtained. The lesions’ pathologic diagnoses will be obtained 2 weeks after the tumor removal. Neurologic function will be assessed using the National Institute of Health Stroke Scale (NIHSS/mNIHSS) at baseline and in the postoperative period. NIHSS scores 15 items including consciousness, visual function, facial and motor function, ataxia, sensory and language function, and attention, and the total score ranges from 0 (no deficit) to a maximum of 42. A modified version of the NIHSS (mNIHSS) abridges to 11 items by deleting level of consciousness, facial palsy, limb ataxia, and dysarthria; the sensory item is collapsed from 3 to 2 choices [15]. Since there is no reliability and validity evidence comparing NIHSS and mNIHSS use in the intracranial tumor population, we will score both as primary outcomes in this study. The scoring system is shown in appendix. Mini-mental state examination (MMSE) will be used to assess the cognitive performance of patients at baseline and after operation. During anesthesia recovery, Anesthesia Recovery Quality and the modified Aldrete scale will be used to assess the recovery condition of patients. Visual Analog Scale (VAS) will be used to assess postoperative pain. QoR-40 (Quality of Recovery from Anesthesia) will be used at 2 days after operation to assess the recovery condition and the satisfaction of the patient related to anesthesia. All adverse events will be recorded. The schedule of data collection is shown in Fig. 1.

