### Statistical analysis plan

Kolmogorov-Smirnov testing will be used for evaluating if the continuous variables have a normal distribution or not. Descriptive statistics will be reported as means with standard deviation for normally distributed data; medians with interquartile range will be described for non-normally distributed data; for categorical variables, count (percentage) will be described. The difference in postoperative NIHSS scores at certain time points between the propofol and sevoflurance groups will be analyzed by t-test or Mann-Whitney U test depending on normal or non-normal distribution, respectively, and 95% confident interval will be determined for the NIHSS score change and difference between the two groups. The changes in VAS scores, intraoperative parameters, and stress response biomarkers over the observation time will be compared using repeated measurement, and post hoc analysis will be used for sensitivity analysis. For other secondary outcomes such as brain relaxation, MMSE score, anesthesia quality score and medical expense, the difference between the two groups will be analyzed by t-test or Mann-Whitney U test. All the categorical variables will be analyzed by chi-square testing. Missing data will be adjusted using inverse probability weighting and worst-case imputation scenarios. Statistical significance is defined as a type I error of 0.05, and the nature of the testing is two-tailed. Analyses will be conducted using Statistical Package for the Social Sciences (SPSS) version 17.0 (Chicago, IL, USA).

All data will be analyzed according to an intent-to-treat, such that all randomized patients originally allocated to the propofol or sevoflurane anesthesia arm at the time of randomization will be used for efficacy analysis. No interim analysis is planned. Worst observation carried forward method will be used to handle missing data.

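### Exclusion criteria cannot make the arms comparable, and the stated NIHSS comparison leaves the recorded lesion site unused, which costs precision but not validity

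*Protocol article*

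**What the plan says.** The Discussion paragraph of the abstract says: "The exclusion criteria are strict to ensure that the groups are comparable in all aspects".

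Other parts of the protocol article bear on this:

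- **Allocation (Randomization and blinding):** "Permuted-block randomization will be used with a block size of 4 and an allocation ratio of 1:1". No stratification factor is named.
- **Eligibility (Populations, Table 1):** frontal, parietal and temporal gliomas are admitted, and "New and/or recurrent intracranial gliomas are allowed". Insular invasion, scheduled motor evoked potential (MEP) monitoring and earlier radiotherapy or chemotherapy are excluded. Exclusion 6 gives tumor location as one example of a definite reason for prolonged emergence.
- **Background:** on reversible deficits seen with supplementary motor area (SMA) lesions, the text says "Although this finding may have been related to lesion location" and adds that a residual anesthetic effect cannot be ruled out.
- **Outcomes:** "Detailed descriptions of the lesion in MRI will be obtained".
- **Statistical analysis plan:** the difference in NIHSS scores between the arms "will be analyzed by t-test or Mann-Whitney U test depending on normal or non-normal distribution", and a "95% confident interval will be determined for the NIHSS score change and difference between the two groups". No covariate is named.

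**The concern.** The sentence in the abstract gives the exclusion criteria a job they cannot do. They decide who may enter. They do not decide how the patients who enter are spread over the two arms.

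What remains after the exclusions is still mixed in lesion site. The primary NIHSS is scored within 4 hours of anesthesia, when a deficit caused by resection at a particular site and a residual anesthetic effect would appear in the same score. Taking the change from baseline removes the preoperative level but not a site-dependent change after surgery: two patients with the same low baseline score may have different expected early deficits.

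The protocol thus points to a plausible prognostic factor and records it before surgery, then fixes a comparison with no place for it. In an equivalence trial the whole interval must lie inside ±1, so variance that could have been explained widens the very quantity that decides the result.

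**Working it through.** **Inputs from the section Sample size calculation:** within-group SD 1.5, assumed true difference 0.5, equivalence margin 1.0, 160 per group, 80% power. The 95% interval comes from the section Statistical analysis plan. The share of variance explained by lesion site (R²) is not in the documents; 5% to 30% is assumed.

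**1. The protocol's own figure.** For the binding side of the two one-sided tests, n = 2 × [SD × (z₁₋α + z₀.₈₀) / (1 − 0.5)]².

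- One-sided 0.025 (95% interval): 2 × [1.5 × (1.960 + 0.842) / 0.5]² = 142 per group after rounding up.
- One-sided 0.05 (90% interval): 112 per group after rounding up.

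Neither equals the stated 160. That is a separate matter, and 160 is kept below because it is the planned number. It errs on the safe side for the stated inputs.

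**2. Unadjusted analysis at 160 per group.**

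- SE = 1.5 × √(2/160) = 0.168.
- 95% half-width = 1.96 × 0.168 = 0.329.
- Power = Φ(0.5/0.168 − 1.96) = 84.6%; the opposite margin contributes essentially nothing.

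**3. Adjusted analysis.** Residual SD = 1.5 × √(1 − R²), put into the same formulas:

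| Assumed R² | Residual SD | 95% half-width | Narrower by | Power at 160 per group | n per group for 80% |
|---|---|---|---|---|---|
| 0 | 1.500 | 0.329 | – | 84.6% | 142 |
| 0.05 | 1.462 | 0.320 | 2.5% | 86.4% | 135 |
| 0.10 | 1.423 | 0.312 | 5% | 88.2% | 128 |
| 0.20 | 1.342 | 0.294 | 11% | 91.5% | 114 |
| 0.30 | 1.255 | 0.275 | 16% | 94.6% | 99 |

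**4. Chance imbalance.** The part of the estimate's 95% range that comes from uneven lesion sites is 0.329 × √R². For R² of 0.10 this is ±0.10 points, and for 0.30 it is ±0.18. These amounts lie inside the ±0.329 and are not added to it.

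**The case against.** The case for leaving the plan alone is strong in several respects, and most of it stands.

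- **Validity.** An unadjusted comparison of randomized arms is unbiased, and its interval already allows for chance imbalance. A reader might infer that uneven lesion sites could pass for an anesthetic effect, or for equivalence, beyond the stated error rate. They cannot.
- **Power.** A reader might infer that the trial is underpowered because site is ignored. The SD of 1.5 is the total within-group SD, so it already contains variation due to site, and power on the stated inputs is above the planned 80%.
- **Size of imbalance.** A large shift is easy to construct. A site present in 30% of patients that adds 3 points would give 1.96 × 3 × √(2 × 0.3 × 0.7/160) = ±0.30. But that factor alone would carry 0.3 × 0.7 × 9 = 1.89 of the total variance of 1.5² = 2.25, or 84%, which cannot be squared with an R² of 30% or less.
- **Recurrence.** Table 1 admits new and recurrent tumors, and a reader might take recurrence as an acknowledged cause of early deficits. No section says so.
- **Evidence on site.** The SMA remark concerns intraoperative deficits in awake craniotomy and is hedged. The insular exclusion removes some site variation. So does the MEP exclusion, since the article's main Discussion ties such monitoring to tumors in or near the motor pathways. Exclusion 6 is itself meant to remove patients whose emergence is affected by location.
- **Condensed article.** A separate analysis plan may name covariates. This article, however, does more than stay silent: it fixes a two-group test for the NIHSS comparison, and neither branch of that test takes a covariate.

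What the objection leaves untouched is that the sentence on comparability is wrong as written, and that a recorded, plausibly prognostic baseline factor goes unused.

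**Conclusion.** The point holds as an overstated sentence together with a missed gain in precision. It is not a flaw that threatens the trial's conclusion.

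How much is lost depends on an R² that the documents do not give. At 5% the gain is slight, under two percentage points of power. At 30% the interval is about a sixth narrower and the chance of missing equivalence when the true difference is 0.5 drops from about 15% to about 5%. These figures assume the protocol's SD, difference and margin, 160 analyzed per arm, and a 95% interval read against ±1. They count lesion site only; any further gain from baseline NIHSS is not quantified here.

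The documents do not support the view that stratified randomization is required. Unstratified blocks are acceptable at this size, and according to Trial status recruitment began in May 2018, so new strata would change the allocation scheme mid-trial.

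**What to change.** 1. Before outcomes are seen by arm, specify that the between-arm difference in NIHSS change is estimated from a linear model with treatment, baseline NIHSS and preoperative MRI lesion site (lobe, plus SMA involvement where the MRI description allows). Read its confidence interval against ±1. Keep the unadjusted interval as a supporting result.
2. Have lesion site coded from the preoperative MRI description by someone blind to allocation. New versus recurrent status may be added as an optional secondary covariate.
3. Reword the abstract so that the exclusions are said to narrow the population, and comparability of the arms is attributed to randomization.

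Cost: a few lines of text, some coding work, and 4 degrees of freedom (baseline 1, three lobes 2, SMA 1), or 5 with recurrence, out of about 320 patients. No new visits or measurements are needed, provided the MRI descriptions are detailed enough. If SMA involvement cannot be coded reliably, lobe alone should be used.

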**Trial registration:**

The study was registered and approved by the Chinese Clinical Trial Registry (Chinese Clinical Trial Registry, ChiCTR-IOR-16009177). Principle investigator: [name] (email address: [contact]) and [name] (email address: [contact]) Date of Registration: September 8th, 2016. Country of recruitment: China.

## Background

According to the statistical report released from Primary Brain and Central Nervous System Tumors Diagnosed in the United States in 2015, thirty out of every 100,000 people in the general population suffered from a primary intracranial tumor requiring craniotomy for tumor resection. Glioma accounted for 60.8% of all primary intracranial tumors [1], of which most of these operations require general anesthesia. These patients have vulnerable central nervous systems because of their intracranial tumors (e.g., gliomas are aggressive lesions that invade central neuronal structures anatomically, and at the neuropathologocial level disturb neuronal connections to impair neural function). Compared to intact brains, neuronal network connection disruptions from intracranial lesions and central nervous system inhibition by anesthetics yield a “double insult” to neurosurgical patients, so to speak, and may make them more sensitive to general anesthesia and surgery, leading to both short and long-term neurologic and neurocognitive dysfunction. Anesthesiologists attempt to choose the anesthetic regimen cautiously, taking into account anesthetics’ effects on cerebral physiology (e.g., intracranial pressure and cerebral perfusion pressure), as well as to minimize the seeming disturbance to neuronal function by facilitating rapid emergence and orientation during recovery. The less postoperative neuronal function is affected by anesthetics, the more accurately the patient’s intracranial disease-related status is reflected, and this is beneficial to neurosurgeons so as to correctly evaluate neural function. The optimal postoperative treatment based on neurological evaluation contributes to reduction of neurologic complications and is critical for long-term quality of life. Therefore, it is important to investigate how different mechanisms of general anesthesia affect postoperative neural function and anesthesia recovery in patients with supratentorial (frontal-parietal-temporal) gliomas in both a qualitative and quantitative (over time) manner, as this may guide anesthetic choice in supratentorial craniotomies for gliomas to ensure a reasonable, safe, and economical perioperative anesthetic regimen.

Inhalational anesthesia and intravenous anesthesia are widely used in current neurosurgical anesthesiology [2], and sevoflurane combined with remifentanil or propofol combined with remifentanil are both accepted as general anesthesia strategies. Comparative studies have been done to investigate the effects of different anesthetics on craniotomies [3], both primary and secondary outcomes focused on the changes in intraoperative physiological parameters [3, 4], laboratory results [3], and anesthesia recovery indices during emergence [5, 6]; however, neuronal disease-specific study is lacking, and there is no evidence related to how postoperative neurological function and neurocognitive outcomes are affected by different general anesthesia strategies [7]. Patients with neurological diseases, e.g., brain tumors, are usually excluded in studies examining the correlation between anesthesia and neural function [8], as those diseases are major confounders leading to nervous system dysfunction, however, anesthetic effects on neural function cannot be ignored in neurosurgical patients, let alone the previously mentioned “vulnerable” brain tumor patient who is even more susceptible to anesthetics [9]. Recent findings have reported patients with supplementary motor area (SMA) lesions presenting with intraoperative neurological deficits for awake craniotomy which could not be explained anatomically by their intact corticospinal tracts as detected by cortical stimulation or cortical mapping [10, 11], and these deficits were reversible after operations over time without further intervention. Although this finding may have been related to lesion location, which is called “SMA symptom”, this phenomenon cannot exclude the possibility of residual anesthetic-induced neurological deficits in both the intraoperative and early postoperative periods.

It has been reported that in some supratentorial brain mass patients, a small plasma concentration of sedative could significantly worsen neurologic deficits before any operative intervention [9], but there is no evidence related to how residual anesthetics affect neurologic deficits after operations. Repeated neurological evaluations after neurosurgeries can help to assess whether surgical interventions are successful and whether long-term neurologic outcomes are primarily related to diseases and surgeries, while short-term neurologic outcomes are subject to perioperative care beyond the above factors; despite only a few hours of surgical intervention for brain tumor, the overlap of general anesthesia and its effects, after surgery is completed, can linger for hours to days, which may worsen neurologic function and confuse providers. However, in the early postoperative stage, it is unknown whether sevoflurane combined with remifentanil and/or propofol combined with remifentanil could result in unexpected neurologic function deterioration, and whether one strategy is inferior or superior to another.

In this study, we will use sevoflurane combined with remifentanil or propofol combined with remifentanil to maintain anesthesia during craniotomy in patients with supratentorial gliomas to determine whether they have comparable effects on neurologic function and neurocognition in the early postoperative period. Since both sevoflurane and propofol are GABAergic anesthetics, we hypothesize that these two general anesthesia methods equivalently affect early postoperative neural function in this group of patients.

